### Statistics

Sample size has been calculated to reach a confidence level of 95% with a power of 80%.

A sample size of 144 patients is calculated supposing that the hospital stay for LC is shorter than 2 days. The sample size will be 72 patients for each group (144 patients for the whole study).

For comparison of the two groups, chi-square analysis and Fisher's exact test are used when appropriate for qualitative data, and the Student t-test (for normal variables) or the Mann Whitney U-test (for nonnormal variables) for quantitative data. For multivariate analysis the stepwise logistic regression is applied. A probability of 0.05 or less is accepted as statistically significant.

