An investigator blinded to the study operation performed, will evaluate postoperative pain intensity on returning to the Surgical Ward (zero time), and after 12 and 24 hours (± 3 hours). The three hours of tolerance (before or after the precise time of control) will be used in order to avoid to awake the patients during the night. But during the day time, if asleep, the patient will be awakened for the pain test. At these timed intervals, the following variable will be recorded: VAS for pain at rest, and on coughing; if, at rest, VAS is more than 3, the patient will be given intravenous 30 mg ketorolac. The pain tests will be also performed whenever the patient ask for additional analgesia between the timed controls and parenteral analgesics will be administered accordingly. Every time the patient undergoes the pain test, he will be asked about the location of pain (in the surgical wound, far from the wound, everywhere or does not know). As soon as patients will begin to drink fluid instead of ketorolac 30 mg iv, they will be offered nimesulide 100 mg 1 tab orally prn (max 2 tabs daily). Orally administered analgesics will be continued in preference to parenterally administered analgesics if they will be efficacious. After discharge, the patients will be offered nimesulide 100 mg 1 tab orally prn (max 2 tabs daily). Also parenteral and oral analgesic drug requirements will be recorded and analyzed as a measure of postoperative pain. Furthermore the patient satisfaction with the analgesia provided (using a scale of poor, satisfactory, good, or excellent) will be recorded before discharge and after 7 days.

Patient discharge will be based on good medical practice criteria: 1) apyrexia 2) absence of diseases requiring hospitalisation 3) return of bowel function 4) patient's compliance.

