### Primary Endpoints

The aim of the study is to compare the results of early laparoscopic and laparotomic cholecystectomy for acute cholecystitis in terms of morbidity, mortality, conversion rate, operation time, hospital stay, postoperative pain, return to normal activity and aesthetic result.

The primary endpoints of our study will be:

To evaluate the value of laparoscopic cholecystectomy to reduce hospital stay

To evaluate the value of laparoscopic cholecystectomy to reduce postoperative pain

To evaluate the conversion rate

The onset of any other complications will be recorded intraoperatively, postoperatively, at discharge, at 7-days, 1-month and 6-months.

All the above mentioned data will be recorded in the Case Report Form and later stored in computer database. At the end of the study the final statistical examination will be carried out.

An interim statistical examination of the data will be done every 3 months during the period of patients' inclusion in the study. Then at the end of every completed follow-up period (1-month, 6-months).

The statistical analysis will be carried out using Epi Info 2000, Version 1.1 software package (Dean AG, Arner TG, Sangam S, Sunki GG, Friedman R, Lantinga M, Zubieta JC, Sullivan KM, Smith DC. Epi Info 2000, a database and statistics program for public health professionals for use on Windows 95, 98, NT, and 2000 computers; Centers for Disease Control and Prevention, Atlanta, Georgia, USA, 2000)

No incentives are planned for the patients regarding the operation or the follow-up.

The study will take approximately 6 months – 1 year for the inclusion period. According to the number of AC menaged monthly in all Centers, the duration of the inclusion period can be approximately of 1 year to reach the number of about 144 enrolled patients.

An interim report is planned at the end of any completed follow-up period.

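### Pain is a primary endpoint with no deciding measure: six scheduled VAS readings and one or two analgesic measures stand unranked against a single per-test threshold of 0.05

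*Protocol article*

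**What the plan says.** The Primary Endpoints section of the protocol article lists three items: hospital stay, pain and conversion rate. The pain item reads in full: "To evaluate the value of laparoscopic cholecystectomy to reduce postoperative pain". It names no time, no condition (rest or cough) and no summary measure.

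The Data Collection section supplies the candidates:

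- Pain is assessed "on returning to the Surgical Ward (zero time), and after 12 and 24 hours", with a tolerance of three hours.
- "At these timed intervals, the following variable will be recorded: VAS for pain at rest, and on coughing".
- Further tests are made whenever the patient asks for more analgesia between the scheduled times.
- "Also parenteral and oral analgesic drug requirements will be recorded and analyzed as a measure of postoperative pain".

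The Statistics section prescribes "the Student t-test (for normal variables) or the Mann Whitney U-test (for nonnormal variables) for quantitative data", and sets the criterion: "A probability of 0.05 or less is accepted as statistically significant". It gives no order among the pain measures, no way to combine them and no sidedness. The sample size is justified by hospital stay alone.

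**The concern.** A primary endpoint should identify the comparison that settles it. Here at least seven comparisons could each be presented as the primary pain result, and each would meet the only criterion stated. This multiplicity lies inside one endpoint and would remain if pain were the sole primary.

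The measures can also disagree. A difference at rest on return to the ward with none on coughing at 24 hours has no pre-set reading. Nor do similar VAS scores with unequal analgesic use. The second pattern is plausible because the protocol ties ward analgesia to the resting score and also gives it on request, so a true difference in pain may appear as a difference in drug use. If the choice of measure is left until the data are seen, the error rate of the pain claim is no longer the stated 5%.

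**Working it through.** **Plan's own figure.** The document states no error rate for the pain endpoint, so there is nothing to reproduce. Its one design figure, "The sample size will be 72 patients for each group (144 patients for the whole study", concerns hospital stay. It comes without a standard deviation and does not bear on this point.

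**Inputs from the document**

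- Scheduled times: 3 (zero time, 12 h, 24 h).
- Conditions per time: 2 (rest, cough). VAS readings: 3 × 2 = 6.
- Analgesic measures: 1 if parenteral and oral use are combined (the text speaks of a single measure), 2 if analysed separately. Total k = 7 or 8; the VAS-only count of 6 is also shown.
- Threshold: 0.05 per test.

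**Assumptions, not in the document**

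- Tests are two-sided, in line with the 95% confidence level used for the sample size.
- Any one significant measure is taken to support the claim.
- The test statistics share a common correlation ρ, shown from 0 to 0.9.
- There is one final look. Unscheduled pain tests are not counted.

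**Step 1: independent tests.** Under no true difference, P(any significant, either direction) = 1 − 0.95^k:

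- k = 6: 1 − 0.95^6 = 26.5%
- k = 7: 1 − 0.95^7 = 30.2%
- k = 8: 1 − 0.95^8 = 33.7%

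P(any significant in favour of laparoscopy) = 1 − 0.975^k:

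- k = 6: 14.1%
- k = 7: 16.2%
- k = 8: 18.3%

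**Step 2: correlated tests.** The statistics were simulated as normal variables with common correlation ρ (400,000 draws per setting). The share of draws with any |Z| > 1.96 gives the either-direction rate. The share with any Z > 1.96 towards laparoscopy gives the false-benefit rate. Each cell shows either direction / favouring laparoscopy.

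| ρ | 6 tests | 7 tests | 8 tests |
|---|---|---|---|
| 0 (step 1) | 26.5% / 14.1% | 30.2% / 16.2% | 33.7% / 18.3% |
| 0.3 | 24.0% / 12.1% | 27.1% / 13.7% | 30.0% / 15.2% |
| 0.5 | 20.8% / 10.3% | 23.0% / 11.5% | 25.0% / 12.5% |
| 0.7 | 16.3% / 8.2% | 17.8% / 8.9% | 19.2% / 9.6% |
| 0.9 | 10.7% / 5.4% | 11.4% / 5.7% | 11.8% / 5.9% |

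**Step 3: a less uniform correlation.** Eight tests were also run with rest–cough correlation 0.6–0.8 at the same time, 0.3–0.6 across times and 0.2–0.4 between VAS and analgesic use. This gives 24–29% in either direction and 12–15% favouring laparoscopy, close to the rows for ρ of 0.3–0.5.

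**Step 4: against nominal.** At ρ = 0.5 the either-direction rate is 20.8/5 = 4.2 to 25.0/5 = 5 times nominal. The false-benefit rate is 10.3/2.5 = 4.1 to 12.5/2.5 = 5 times nominal. At ρ = 0.9 the smallest ratios are 10.7/5 = 2.1 and 5.4/2.5 = 2.2.

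**Step 5: after the change.** One pre-named contrast tested once at two-sided 0.05 gives 5% in either direction and 2.5% favouring laparoscopy.

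**The case against.** **The article is condensed.** The choice of summary measure and the handling of multiplicity often sit in an analysis plan, and one may exist. This stands as far as adjustment methods go, and their absence is not the point made here. But what the primary endpoint is belongs in the protocol. This article gives the pain schedule at length, adds a second kind of pain measure for analysis, and states its tests and threshold, yet leaves the endpoint open.

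**The rule that any one result suffices is not stated.** This is correct. No sentence says that each reading will be tested separately, or that one significant reading is enough. A single per-patient summary tested once would also fit the Statistics section. The rates above therefore describe what the text permits.

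**A false benefit of laparoscopy.** A reader might infer that reduced pain could be claimed falsely 20–25% of the time. The document does not support that. Those figures count differences in either direction, and with two-sided tests the rate favouring laparoscopy is about half. If the tests were one-sided at 0.05, it would be 18.5–21.9% at ρ = 0.5 (against 5% nominal), but no sidedness is stated.

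**Later cough scores as the clean measure.** A reader might also infer that cough scores at 12 and 24 hours escape the effect of analgesia. They do not. Ward analgesia may be given from the zero-time reading onward and on request between readings, and nothing in the text shields cough scores from it. Analgesic use must therefore be read beside any VAS contrast.

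**Conclusion.** The point holds as a badly fixed primary endpoint: pain is primary, seven or eight measures could decide it, and none is chosen. Across six to eight tests, if any significant measure may support the claim, tests are two-sided and ρ is 0.5:

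- a false pain difference in either direction has probability of about 21–25% (about 11–12% at ρ = 0.9, 27–34% at ρ = 0);
- a false benefit of laparoscopy has probability of about 10–12.5% against 2.5% nominal (about 5–6% at ρ = 0.9, 14–18% at ρ = 0).

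The correlation and the decision rule are assumptions, but the inflation is at least about twofold across the range shown. That the measure is undefined does not depend on either assumption. The change should be made; it does not call the design into question.

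**What to change.** In the Primary Endpoints and Data Collection sections, name one deciding pain contrast before data are seen. One example is the between-arm difference in VAS on coughing, averaged over the 12 h and 24 h tests, as one score per patient and one test at 0.05. Another single contrast named in advance would control the error equally well. Label the other VAS readings as supportive, with no significance claim. Report analgesic requirement by arm beside the deciding contrast, because the 12 h and 24 h scores are taken after ward analgesia and a true difference may show up there instead.

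The cost is a few sentences: the data are already scheduled, and no extra patients or visits are needed. The downside is that an isolated effect at one time point, only at rest, or only in analgesic use can no longer be claimed as the primary pain result.

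This controls error within the pain endpoint only. The three-monthly interim examinations and the other two primary endpoints are separate matters.

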## Methods

### Design

The study project is a prospective, randomized investigation. The study will be performed in the Department of Emergency Surgery St Orsola-Malpighi University Hospital (Bologna, Italy), a large teaching institutions, with the participation of all surgeons who accept to be involved in (and together with other selected centers).

The patients will be divided in two groups: in the first group the patient will be submitted to early LC (Laparoscopic Cholecystectomy) within 72 hours after the diagnosis of cholecystitis while in the second group will be submitted to early LTC (LaparoTomic Cholecystectomy) within 72 hours after the diagnosis.

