#### Data Collection

Patients' data sheets are generated containing demographic data and preoperative, operative, and postoperative information.

Pre-operative notes concern the history of gallbladder stones, the presence of associated diseases (cardiac, hypertension, diabetes, malignancy), duration of gallbladder complaints (as an indication for the onset of the disease), finding of a palpable gallbladder, temperature, and laboratory results of WBC count, serum bilirubin, gamma GT, PCR, IL-6 and alkaline phosphatase. Ultrasound findings are also reported.

Operative data of concern are macroscopic findings (of acute cholecystitis, gangrenous cholecystitis, hydrops, and empyema of the gallbladder), the presence of small stones (< 1 cm diameter) or large bile stones (> 1 cm diameter), information regarding perforation of the gallbladder and intraperitoneally "lost" stones, reasons for conversion, and duration of surgery. Postoperative notes of interest included the use of nasogastric tubes and drains, the amount of analgesics used, (evaluation of pain with VAS score), complications, and length of hospital stay.

Complications are classified as surgical infections (wound infection, subphrenic or subhepatic abscess); noninfectious surgical problems (e.g., bile duct injury, hemorrhage); remote infections (urinary or respiratory); and miscellaneous problems (e.g., atelectasis, deep vein thrombosis, AMI, CVA, etc). The collected information are entered into a database as either continuous or categorical variables for statistical analysis. Following the operative procedure, a large sterile dressing will be applied to cover the entire abdomen.

A second surgical team, aware of the operative findings but not the surgical access approach, then will assume the care of the patient. Postoperative care and ability to be discharged from the hospital will be determined by the second surgical team. This second surgical team will be blinded to the surgical approach. The primary operative team will be in every moment available for emergent consultation or evaluation of the wound.

In the pre-anaesthetic holding area, baseline pain will be investigated at rest and on coughing using a pain-rating scale systems: a 100-mm visual analogue scales (VAS) (0 = minimal and 100 = maximal).

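### The ketorolac trigger of VAS above 3 has no unit and does not fit the only pain scale the protocol defines, which runs from 0 to 100 mm

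*Protocol article*

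**What the plan says.** All the relevant text on scoring and dosing is in the protocol article under Data Collection.

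- **Scale.** Before anaesthesia, "baseline pain will be investigated at rest and on coughing", using "a 100-mm visual analogue scales (VAS) (0 = minimal and 100 = maximal". No other pain scale is defined in the document.
- **Postoperative tests.** A blinded investigator assesses pain "on returning to the Surgical Ward (zero time), and after 12 and 24 hours", and records "VAS for pain at rest, and on coughing".
- **Dosing rule.** At these tests, "if, at rest, VAS is more than 3, the patient will be given intravenous 30 mg ketorolac". No unit is given.
- **Switch to oral treatment.** "As soon as patients will begin to drink fluid instead of ketorolac 30 mg iv, they will be offered nimesulide 100 mg", as needed.
- **Use in the analysis.** "parenteral and oral analgesic drug requirements will be recorded and analyzed as a measure of postoperative pain".

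Primary Endpoints lists reduction of postoperative pain as one of three primary endpoints. Design says the study runs at the Bologna hospital "together with other selected centers".

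**The concern.** A threshold of 3 makes clinical sense on a 0–10 scale. On a scale anchored at 0 and 100 it is almost the floor. The protocol prints the second scale and a number that suits the first, and says nothing to reconcile them.

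This matters because the number is a drug-administration rule. Staff who have just scored baseline pain from 0 to 100 are told to act above 3. If they follow the text, they give an intravenous NSAID for trivial pain. If they assume a change of unit, they wait until 30 mm.

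The dose given then counts as outcome data, since analgesic requirement is analysed as a measure of pain. If centres were to read the trigger differently, part of the variation in that measure would come from the reading and not from the patients.

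**Working it through.** There is no calculated figure in the plan to reproduce. The check compares the trigger with the defined scale and assumes no distribution of pain scores.

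**Inputs (all from Data Collection)**

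| Input | Value |
|---|---|
| Scale length and anchors | 100 mm, 0 to 100 |
| Trigger at rest | above 3, no unit |
| Timed tests | 0, 12 and 24 h, so 3 |
| Ketorolac dose | 30 mg IV |

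**Step 1: does the defined scale apply after surgery?** The text attaches the 100 mm scale to the baseline measurement, so carrying it to the ward tests is an inference. It is supported by the same abbreviation, the same two conditions (at rest and on coughing), and the absence of any second scale.

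**Step 2: the two readings as a share of the range.**

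- Literal: 3 / 100 = 3%.
- As 3 on a 0–10 scale: 3 × 10 = 30 mm, and 30 / 100 = 30%.
- Ratio: 30 / 3 = 10.

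**Step 3: where the readings give opposite orders.** They disagree for scores above 3 mm and up to 30 mm, a band of 30 − 3 = 27 mm. In whole millimetres there are 101 possible scores (0 to 100):

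- above 3: scores 4 to 100 are dosed, 97 values;
- above 30: scores 31 to 100 are dosed, 70 values;
- difference: 97 − 70 = 27 values (4 to 30).

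This describes the width of the scale affected. The document gives no pain distribution, so the share of patients in the band is unknown.

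**Step 4: largest difference for one patient from the timed rule.** Suppose the resting score lies in the band at all three tests and the patient is not yet drinking.

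- Literal reading: 3 × 30 mg = 90 mg.
- 0–10 reading: 3 × 0 mg = 0 mg.

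This is an upper bound, not an expected value. Doses given on request between the timed tests and oral nimesulide are not counted.

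**The case against.** The best case for the text has four parts.

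- **It is a condensed article.** The unit may be printed on the case report form. That could excuse a missing unit alone. It does not excuse a printed threshold that fails to fit a printed scale.
- **The 100 mm definition belongs to baseline.** This is true of the wording, and the contradiction therefore rests on a short inference. But if the ward tests used a different scoring, the protocol would contain two VAS scales with one undefined, and that would need correcting too.
- **Clinicians will read it as 3 out of 10.** A 100 mm line is 10 cm long, so this reading is natural. If everyone adopts it, only the wording is wrong. This part stands, and it is the main reason the point is minor.
- **The consequences are limited and partly conjectural.** Nothing in the document shows that centres would differ. Pain is also scored directly, and analgesic use is an additional measure. The switch to oral treatment may make the rule inactive at 12 or 24 h, so the 90 mg bound may rarely be approached. All of this stands, so divergence between centres and its effect on the pain endpoint are possibilities only.

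**Conclusion.** The concern holds, as a minor inconsistency. The trigger has no unit, and 3 does not fit the only scale defined. The text does not settle whether the threshold is 3 mm or 30 mm, although 30 mm is probably meant. The finding rests on one inference, that the baseline scale is also the postoperative scale.

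The rule is identical in both arms and is applied by a blinded assessor, so it does not in itself bias the comparison. The sample size rests on hospital stay (Statistics) and is not affected. What remains is an operative dosing rule that is wrong if followed literally, and a possible source of avoidable variation in a measure of a primary endpoint.

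**What to change.** Ask the clinical investigators to confirm the intended threshold. If it is 3 on a 0–10 scale, as seems likely, reword the rule along these lines:

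> Ketorolac 30 mg IV is given when the resting score exceeds 30 mm on the 0–100 mm VAS.

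State that all baseline and postoperative VAS scores are recorded in millimetres from 0 to 100 at every centre. The cost is a one-line clarification, with no change to the sample size, the visit schedule or the data collected.

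### The two-branch test rule has no place for ordered categories, so satisfaction with analgesia most naturally goes to a test that ignores their order

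*Protocol article*

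**What the plan says.** Under Data Collection, the protocol article has patients rate their satisfaction with the analgesia "using a scale of poor, satisfactory, good, or excellent". The rating "will be recorded before discharge and after 7 days". The four words run from worst to best.

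The Statistics section sorts comparisons of the two groups into two branches. In the first, "chi-square analysis and Fisher's exact test are used when appropriate for qualitative data". In the second, Student's t-test is used for normal variables and "the Mann Whitney U-test (for nonnormal variables) for quantitative data". No trend test or other method for ordered categories is named. On significance the section says: "A probability of 0.05 or less is accepted as statistically significant".

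Data Collection also says how the collected information is typed: it is "entered into a database as either continuous or categorical variables for statistical analysis". There is no third, ordinal type.

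Satisfaction is not among the three primary endpoints listed under Primary Endpoints (hospital stay, postoperative pain, conversion rate), nor in the broader list of aims in that section. The planned size is 72 patients per group, 144 in all, and rests on hospital stay.

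**The concern.** A verbal four-level rating is not a continuous measurement. Under the typing in Data Collection it is categorical, and under the rule in Statistics categorical data go to chi-square or Fisher. On a 2×4 table the Pearson test has 3 degrees of freedom and gives the same p-value if the four labels are shuffled. Fisher's exact test on the same table is equally blind to order.

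Two things are at stake. If one operation leaves patients generally more satisfied with their pain relief, an order-blind test is less likely to detect it. And a significant result need not mean that either arm did better, since it can arise from a difference in spread alone.

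**Working it through.** **Inputs from the protocol article.** 72 patients per group; four ordered levels; significance at 0.05 (sidedness not stated; two-sided assumed here).

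**Inputs that must be assumed.** The article gives neither a level distribution nor an expected effect for satisfaction. Five control-arm distributions (poor/satisfactory/good/excellent, %) were tried: 25/25/25/25, 10/30/40/20, 5/20/45/30, 20/40/30/10 and 5/15/40/40. Odds ratios ran from 1.5 to 4.

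**The plan's own figure.** The only power figure concerns hospital stay. Reading the assumption as a 2-day difference, 72 per group with 80% power at two-sided 0.05 implies a standardised effect of (1.960 + 0.842) × √(2/72) = 0.467, so an SD of 2/0.467 = 4.28 days. No SD is stated, so 144 can be neither confirmed nor refuted. There is no power figure for satisfaction to reproduce.

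**Step 1: the shift.** Under proportional odds, each cumulative odds in the control arm is divided by the odds ratio. For 10/30/40/20 and odds ratio 2:
- control cumulative proportions 0.10, 0.40, 0.80 have odds 0.111, 0.667, 4;
- halved: 0.056, 0.333, 2;
- back to cumulative proportions: 0.053, 0.250, 0.667;
- other arm: 5.3/19.7/41.7/33.3%.

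**Step 2: the two tests.** With n = 72 per arm, N = 144 and column totals t:
- Pearson: X² = Σ(a − b)²/t, on 3 df.
- Tie-corrected Mann-Whitney: z = (W − n(N+1)/2)/√V, with V = (n²/12)[(N+1) − Σ(t³ − t)/(N(N − 1))].

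**Step 3: hand check of the chi-square power.** The noncentrality is n Σ(p₁ − p₂)²/(p₁ + p₂) = 72 × (0.0147 + 0.0212 + 0.0003 + 0.0333) = 72 × 0.0695 ≈ 5.0. A 3-df test has 43.2% power at noncentrality (1.960 + 0.253)² = 4.90, which agrees with the simulated 44.1% below.

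**Step 4: simulation, 20,000 trials per setting.** Power in %, gaps in percentage points taken before rounding:

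| Odds ratio | Chi-square, 10/30/40/20 | Mann-Whitney, 10/30/40/20 | Gap | Gap over all five distributions |
|---|---|---|---|---|
| 1.5 | 17.0 | 26.5 | 9.5 | 8.6 to 9.6 |
| 1.75 | 29.6 | 44.6 | 15.0 | 14.8 to 15.2 |
| 2 | 44.1 | 61.7 | 17.6 | 17.2 to 18.2 |
| 2.25 | 57.5 | 74.7 | 17.2 | 16.7 to 17.8 |
| 2.5 | 69.4 | 84.1 | 14.8 | 14.1 to 15.8 |
| 3 | 85.8 | 94.3 | 8.5 | 8.3 to 10.7 |
| 4 | 97.2 | 99.4 | 2.1 | 1.8 to 3.5 |

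With no difference between arms, the rejection rates for 10/30/40/20 are 5.0% and 4.9%, so the gap does not come from a liberal test.

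**Step 5: check without a level distribution.** At equal noncentrality, a 1-df test with 80% power has noncentrality (1.960 + 0.842)² = 7.85. Spread over 3 df, the same noncentrality gives 64.5%, a loss of 15.5 points. From 60% the loss is 16.8 points, and from 95% it is 7.9.

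**Step 6: differences without a uniform shift.** For 10/40/40/10 against 25/25/25/25, chi-square has 91.5% power and Mann-Whitney 5.6%. The arms differ in spread, but neither is more satisfied on the whole.

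Where the lowest level is rare, small expected counts are common: with 5/20/45/30 and odds ratio 2, 95% of tables have at least one below 5. Fisher's test would then be the likelier choice. It too ignores order, but its power was not computed here.

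**The case against.** The strongest reply is that the article never assigns a test to satisfaction. The Statistics section is a short general menu, its first branch is qualified, and the sentence on variable types stands in a paragraph about complications and concerns database entry. A score stored as categorical can still be compared by ranks. Analgesic use is said to be recorded and analysed, whereas satisfaction is only said to be recorded. An analysis plan that is not shown may settle the matter.

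Much of this stands. A reader might infer that the protocol prescribes chi-square for satisfaction. It does not; that is the most natural reading of two general sentences. The qualifier in the first branch, however, most naturally governs the choice between chi-square and Fisher, and the second branch is reserved for quantitative data. A reader who follows the printed rule is therefore led to an order-blind test. The criticism is of a rule that is stated and fits this variable badly, not of missing detail.

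Two other readings go too far. One is a fixed loss of 15 to 18 points: that describes a moderate uniform shift only, and the article gives no effect or distribution that would place satisfaction there. The other is that a rank test costs nothing: Step 6 shows that chi-square can be far more powerful when the arms differ in spread.

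**Conclusion.** The point holds as a minor one. As written, the rule has no ordinal category, and the satisfaction scale most naturally falls to tests that do not address whether one arm is more satisfied. If chi-square is used, the loss against a tie-corrected Mann-Whitney test is roughly 2 to 18 percentage points over odds ratios of 1.5 to 4. It is largest near an odds ratio of 2 and smaller on either side.

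These figures assume 72 evaluable patients per arm, a two-sided 0.05 level, a proportional-odds shift and level distributions that the article does not supply. Nothing here bears on the three primary endpoints or on the sample size. The trial never claimed a given power for satisfaction, so no promised power is broken.

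**What to change.** Add one sentence to the Statistics section: ordered categorical outcomes, such as satisfaction with analgesia before discharge and at 7 days, are compared between groups by the Mann-Whitney test with correction for ties (or by a proportional-odds model), and the full distribution over the four levels is tabulated by group.

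The Mann-Whitney test is already in the plan, so no new data, visits or patients are needed. The cost is lower sensitivity to a difference in spread without a directional shift; the tabulation keeps such a pattern visible. If an analysis plan already says this, the two documents need only be aligned.
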